### Participants

The study population consists of twins and singletons born from IVF between 2003 and 2005, of whom parents have received IVF treatment in one of the five participating IVF centres in the Netherlands (Academic Medical Centre, Maastricht University Medical Centre, Radboud University Nijmegen Medical Centre, Erasmus Medical Centre and University Medical Center Utrecht). In the Netherlands, subfertility care is well-organized and centred in thirteen licensed clinics [52]. Hospitals without a licence can initiate and monitor the stimulation phase and refer to a licensed hospital for both oocyte retrieval and embryo transfer (satellite clinics) or for embryo transfer alone (transport clinics). Five of the 13 licensed centres and their collaborating transport- and satellite clinics, participate in the TwinSing study.

The *full sample *consists of all IVF twins and IVF singletons born between 2003 and 2005 of whom parents have received treatment in one of the participating centres. A total of 4,809 ongoing pregnancies were reported by these IVF centres between 2003 and 2005, of which - 3,789 singleton and 1,020 twin pregnancies. The actual size of the full sample will be somewhat lower since the reported figures are indicative; they are based on ongoing pregnancies not live births. Inclusion of an older cohort of IVF children is not considered to be valid, since the quality and results of IVF, neonatal and paediatric care have improved considerably during the last decade and since this study relies heavily on retrospective data collection, both from existing registries as well as from parents.

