**Figure 1 F1:**
[figure not shown]
**Risk stratification and sample size (figures are indicative)**.

In order to sufficiently take account of heterogeneity within the children who experienced health problems, it is expected that costs and outcome data of at least 100 singletons and 100 twin children with health problems are required in the reduced sample. Regarding children without health problems, data of 50 singletons and 50 twin children is expected to be sufficient, as variance will be considerably lower. Taking sufficiently account of missing data in all phases of data collection (5% for risk stratification, 10% for data collection up to one year of life and 20% for data collection up to five years of life), a sample size of 175 twin children with health problems, 56 twin children without health problems, 104 singletons with health problems, and 56 singletons without health problems, is required for the reduced sample.

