#### Risk stratification

Risk stratification will be applied to all children in the full sample. Based on information from the PRN regarding the pregnancy (weeks gestation) and the newborn (birth weight, Apgar score and congenital malformations), the children of the full sample will be assigned to a risk profile (i.e. 'low risk', 'moderate risk' or 'high risk'). The risk stratification criteria are: 1) prematurity (< 37 weeks gestation); 2) 5-minute Apgar score (< 7); 3) congenital malformations; and 4) birth weight (< 2,000 gram) (see figure 1). The criteria are set such that the probability of a false negative, i.e. the chance that a child 'at risk' is assigned to the low risk category, is minimized. A child will be assigned to the 'moderate risk' category if the child is born before 37 weeks gestation, has a Apgar score below seven, or has a congenital malformation. If the child also has a birth weight below 2,000 gram, the child will be assigned to the 'high risk' category. The other children will be assigned to the 'low risk' category. Based on figures reported by the PRN [12] and expert opinion it is expected that approximately 8% of the singletons will be assigned to the 'moderate risk' or 'high risk' category. All 'moderate risk' and 'high risk' singletons and a random selection of 10% of the remaining ('low risk') singletons will be included in the base sample. Based on figures reported by the PRN [12] and expert opinion it is expected that half of the twin children is born before 37 weeks gestation, have a low APGAR score or a congenital malformation. Approximately 40% of these twin children will also have a low birth weight (20% of all twin children) and will be assigned to the 'high risk' category. The other 60% of these twin children will have a birth weight above 2000 gram (30% of all twin children) and will be assigned to the 'moderate risk' category [12]. All other children (50% of all twin children) will be assigned to the 'low risk' category. All twin children of the 'high risk' category, a random selection of 30% of the 'moderate risk' category and a random selection of 10% of the 'low risk' category will be included in the base sample.

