#### Empirical data collection up to the first year of life

Data with respect to the first year of life will be collected in children of the base sample. Based on figures reported by the PRN over 2004 [12] and expert opinion it is expected that approximately 1,278 children will be included in the base sample. The estimated number of children in each risk category is shown in figure 1.

Cost and outcome data up to the first year of life will be obtained from the hospital information systems of the relevant hospitals, existing registries and, if necessary, patient charts will be reviewed to obtain relevant cost and outcome data. The following registries will be used: 1) the PRN, which encompasses information regarding mother, pregnancy and the newborn; 2) the National Medical Registration (LMR), which registers medical and administrative data of all patients who have been admitted or have received outpatient treatment in Dutch hospitals; and 3) the Netherlands Twin registry (NTR), which follows a cohort 72,000 twins regarding pre- and perinatal information, health status, growth and motor development and behaviour [53,54]. As we intend to collect follow up data directly from hospital records, the use of data from the LMR will be optional. It is expected that data collection up to the first year of life will succeed in 90% of these children.

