#### Empirical data collection from the first year of life up to the fifth year of life

Based on empirical collected costs and outcome data up to the first year of life, a subgroup of children will be selected for data collection up to the fifth year of life, referred to as the reduced sample. All children with resolved or persistent health problems, and a random sample of children without resolved or persistent health problems will be included in the reduced sample. Assuming that missing data are completely at random, resolved and persistent health problems are expected in 4.0% of the singletons and in 12.5% of the twin children. Approximately 488 children will be included in the reduced sample (see figure 1). Besides the data sources mentioned above, cost and outcome data up to the fifth year of life will also be gathered by means of a parent questionnaire. The questionnaire will consist of three parts, the first part referring to the past, the second part referring to the present and the third part referring to expectations regarding the future. The parent questionnaire will focus on health outcomes, HRQoL and costs.

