### Data analysis

#### Empirical data

Health outcomes of the singleton and twin children, including mortality, perinatal outcomes, morbidity and developmental and behavioural problems will be analysed. Subsequently, health outcomes will be expressed in QALYs. QALYs will be calculated based on mortality and HRQoL data retrieved from both the EQ-5D and the HUI. Costs will be calculated by multiplying volumes of resource use with the cost price. Cost prices will be obtained from the Dutch manual of costing studies [60] and financial departments of the participating centres. For cost prices that are not readily available, such as institutional care, special education and school absence, cost price calculations will be performed.

Descriptive statistics will be used to describe the main characteristics and outcomes of IVF singleton and twin children. The base sample and the reduced sample are not representative of the Dutch IVF population as a consequence of the risk stratification and the random selection of subsamples of healthy children. Therefore, before analysing the data, the proportions of high, moderate and low risk singletons and twin children will be adjusted, to properly reflect the ratios in the original population.

Results will be presented with and without stratification for maternal age and parity. The issue of selection (information) bias will be investigated explicitly by comparing PRN data of children with (completely) missing data with PRN data of children included in the analysis.

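### Beyond risk-class adjustment, loss by age five is only described with birth-registry data; the first-year health and cost data held on every child lost at that stage are not used

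*Protocol article*

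**What the plan says.** All references are to the protocol article.

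- **Planned loss** (Participants, sample-size paragraph under Figure 1): "5% for risk stratification, 10% for data collection up to one year of life and 20% for data collection up to five years of life". The section on first-year data collection agrees on its stage: "It is expected that data collection up to the first year of life will succeed in 90% of these children".
- **Planning assumption** (Empirical data collection from the first year of life up to the fifth year of life): the expected frequencies of health problems, 4.0% of singletons and 12.5% of twin children, are introduced with "Assuming that missing data are completely at random".
- **Selection of the five-year sample** (same section): it is drawn on first-year cost and outcome results. All children with resolved or persistent problems enter, plus a random sample of the others. A parent questionnaire is then added to the hospital and registry sources.
- **Check on bias** (Data analysis, Empirical data): "The issue of selection (information) bias will be investigated explicitly by comparing PRN data of children with (completely) missing data", set against the PRN data of children included in the analysis.
- **Adjustment** (same section): before analysis, the risk-class proportions of singletons and twins are restored to those of the original population. The reasons given are the risk stratification and the subsampling of healthy children. Non-response is not mentioned.

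**The concern.** A comparison can show that responders differ from non-responders, but it does not remove the difference. The one named here also looks only at birth-registry variables. By the five-year stage the study knows more about each child: whether a health problem occurred in the first year, and what care cost in that year. Both are likely to predict later cost and quality of life better than birth data, and they may predict whether a parent responds.

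Completely random loss is not obvious here. Quality of life is a parental proxy rating, and the questionnaire needs signed consent (Ethical considerations). The background section on parents' lives reports more stress and depression in mothers of IVF twins. The Discussion says that most problems and costs arise in a small group of children, so selective loss or selective response in that group carries extra weight.

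The five-year estimates feed the 18-year model and the comparison of single with double embryo transfer. The Problem definition also asks for an estimate that takes sources of bias into account.

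**Working it through.** **1. The plan's own figures reproduce.** Inputs: "3,789 singleton and 1,020 twin pregnancies" (Participants), so 1,020 × 2 = 2,040 twin children; "approximately 8% of the singletons will be assigned to the 'moderate risk' or 'high risk' category", all selected, plus 10% of low-risk singletons; for twins, all of the high-risk class (20% of twins) and "a random selection of 30% of the 'moderate risk' category and a random selection of 10% of the 'low risk' category" (30% and 50% of twins).

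- Singletons: 3,789 × 0.95 = 3,600; × (0.08 + 0.92 × 0.10) = 619.
- Twin children: 2,040 × 0.95 = 1,938; × (0.20 + 0.30 × 0.30 + 0.50 × 0.10) = 659. Total 1,278, as stated.
- With problems after the first-year stage: 0.040 × 3,600 × 0.90 = 130 singletons; 0.125 × 1,938 × 0.90 = 218 twin children.
- Adding 70 per group without problems (inferred from 56/0.80) gives 200 and 288, total 488, as stated.
- After × 0.80: 104, 174, 56 and 56. The article has 104, 175, 56 and 56, which sum to 391.

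**2. Who is lost, and what is known about them.** At the five-year stage 488 − 391 = 97 children are lost. All were selected on first-year results, so all have PRN and first-year data. Over all stages, planned loss is 1 − 0.95 × 0.90 × 0.80 = 31.6%:

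| Stage | Loss | Data held |
|---|---|---|
| Risk stratification | 5.0% | no usable risk data |
| To year 1 | 0.95 × 0.10 = 9.5% | PRN only |
| Years 1 to 5 | 0.95 × 0.90 × 0.20 = 17.1% | PRN and first year |

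So (9.5 + 17.1)/31.6 = 84% of all losses have PRN data, and 17.1/31.6 = 54% have both.

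**3. What the planned adjustment does correct.** Assume, for twins, loss of 30/20/16% and health problems in 35/10/5% of the high/moderate/low classes (not in the article). Overall loss is 0.2 × 30 + 0.3 × 20 + 0.5 × 16 = 20%. True frequency is 0.2 × 35 + 0.3 × 10 + 0.5 × 5 = 12.5%. Without reweighting, responders give (0.2 × 0.70 × 0.35 + 0.3 × 0.80 × 0.10 + 0.5 × 0.84 × 0.05)/0.80 = 11.75%. Restoring the risk-class proportions gives 12.5% again.

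**4. What it cannot correct.** Suppose instead that loss depends on health-problem status within a risk class. Let p be the true proportion with problems, r the ratio of loss with problems to loss without, and 20% the overall loss, with sampling fractions already accounted for. Loss without problems is l = 0.20/(1 − p + rp). The proportion represented among responders is q = p(1 − rl)/0.80. Example, twins, r = 2: l = 0.20/1.125 = 0.178; q = 0.125 × (1 − 0.356)/0.80 = 10.1%.

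| r (assumed) | Twins, true 12.5% | Singletons, true 4.0% |
|---|---|---|
| 0.5 | 14.0% | 4.5% |
| 0.8 | 13.1% | 4.2% |
| 1.25 | 11.8% | 3.8% |
| 1.5 | 11.2% | 3.5% |
| 2 | 10.1% | 3.1% |

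The table treats each plurality group as one class. The resulting error in a five-year mean is (q − p) times the difference in mean between children with and without problems, and the article does not give that difference.

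**The case against.** **A condensed article need not name its missing-data method.** True, and silence on imputation or response weights would be no finding. But the article is not silent. It states a check and an adjustment, and both are confined to birth-registry information at a stage where better information is held by design. That can be judged as written.

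**The loss is already corrected.** Partly right. Adjustment to risk-class proportions, separately for singletons and twins, acts as post-stratification if applied to the children analysed (step 3). A reader might infer that loss is never corrected; the article does not support that. The subsampling of healthy children is also among the reasons given. If the sponsor means to restore the proportions with and without first-year problems among responders too, much of the remaining gap closes. What the text says will be adjusted, however, is the risk-class proportions only.

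**The random-missingness phrase is only for planning.** Right. It qualifies the expected frequencies behind the sample size and declares no analysis assumption.

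**Non-response to the questionnaire is not loss of all cost data.** Right. Hospital systems, registries and charts remain sources up to age five, and consent is tied to the questionnaire. The concern therefore bears mainly on quality of life and non-hospital costs.

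**A numerical cost bias cannot be claimed.** Right. A reader might reason that if children lost cost 1.25, 1.5 or 2 times as much as those retained, the mean is 4.8%, 9.1% or 16.7% too low, from 1/(0.8 + 0.2m) − 1. Those ratios are not in the article and all point one way, although parents of ill children may respond more readily. The sum also ignores the risk-class adjustment and surviving hospital data. Nor does a response rate that merely differs between twins and singletons bias means estimated within each group.

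**Conclusion.** The point holds in a limited form. Beyond the risk-class adjustment, loss is only described, and only with PRN data. First-year health-problem status and costs, available for all of the roughly 97 children expected to be lost at the five-year stage, serve neither to detect nor to correct it. Loss related to first-year health within a risk class therefore stays uncorrected, mainly for parent-reported quality of life and non-hospital costs.

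Size and direction cannot be derived from the document; the table in step 4 is illustrative and runs both ways. The conclusion rests on two readings: that the risk-class adjustment is applied to the children analysed, and that it does not already include first-year status. The 20% concerns the last stage only. The 31.6% is cumulative, and the remedy for five-year loss does not reach children lost earlier, who have PRN data at most.

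**What to change.** - For five-year outcomes, extend the planned weighting so that it also adjusts for non-response by first-year health-problem status, within plurality and risk class. Add first-year cost where numbers allow. Alternatively, use multiple imputation with the same variables for partly missing records.
- Include first-year health status and cost in the comparison of children with and without five-year data.
- Report the result weighted by risk class only as a sensitivity analysis.

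The cost is slightly more analysis and somewhat more variable weights. Small cells may need to be merged. No new data are required.

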#### Development TwinSing model

A prognostic model will be developed which estimates the short and long-term costs and health outcomes of IVF singletons and IVF twin children. The structure and modelling method of the TwinSing model will be determined in close cooperation with experts in the project team and the participating centres. We expect that a Markov model will best suit the data; however, the final decision regarding which modelling method to use will be made after data become available.

#### Short and long-term cost-effectiveness of SET strategies versus DET strategies

The TwinSing model will be linked to a short-term Markov model developed at the University Hospital Maastricht [32], that compared seven embryo transfer strategies varying from three cycles SET to three cycles DET and several combination strategies. Parameter values were based on data from a large randomised controlled trial in which patients who started their first IVF cycle in the Maastricht University Medical Centre were included.

The economic evaluation will be performed from both the societal and the health care perspective and the time horizon will be 18 years. Cost and benefits occurring after one year will be discounted according to national guidelines [61].

The ultimate model - in which the short-term Markov model and the TwinSing model have been integrated - will enable the estimation of the cost-effectiveness of SET strategies versus DET strategies, expressed as the additional costs per life year gained and the additional costs per QALY. The cost-effectiveness will be analysed using a short term time frame (1-year) and a long term time frame (5 and 18-year).

Uncertainty in the model will be investigated by one-way sensitivity analysis and probabilistic sensitivity analysis. One-way sensitivity analysis will be used to test the robustness of the results for (methodological) uncertainties (e.g. discount rate and health-related quality of life instrument used). Parameter uncertainty will be further tested using probabilistic sensitivity analysis. Distributions will be fitted for all parameters in the model, except fixed parameters. Beta distributions will be fitted for probabilities and gamma distributions will be fitted for costs. Net monetary benefits (NMB) will be calculated for each strategy and cost-effectiveness acceptability curves (CEACs) will be constructed. CEACs provide a graphical representation of the probability that a strategy is cost-effective for a range of ceiling ratios. Subsequently, the cost-effectiveness acceptability frontier (CEAF) will be established, to indicate the preferred strategy.

As most parents prefer a complete family instead of one child, a secondary analysis will be performed in which the cumulative pregnancy rates and live birth rates of subsequent IVF treatments (up to three) will be estimated. Doing so, the costs and outcomes of children of the second or third IVF treatment will be evaluated to estimate the cost-effectiveness of SET strategies versus DET strategies.

#### Value of information analysis

Inherent to modelling is that results are surrounded by an amount of uncertainty. Value of information analysis addresses the issue whether the most efficient embryo transfer strategy can be adopted based on the available knowledge after finishing this study or whether more evidence is required [62-65]. An expected value of perfect information (EVPI) analysis will be performed, which draws on the probabilistic model developed in this study. Subsequently partial EVPIs will be calculated to identify the parameters for which more accurate estimates are the most valuable and which should be the focus of future research.

### Ethical considerations

The study protocol has been reviewed and approved by the Medical Ethical Committee of the Maastricht University Medical Centre (MUMC). Parents will be informed in written format about the TwinSing study and are asked to return a signed informed consent form if they decide to participate in the parent questionnaire.

## Discussion

Multiple pregnancies are regarded as a complication of IVF. To date, SET is more and more accepted as the solution for the high frequency of twin pregnancies after IVF. To support the claim that twin pregnancies are a complication of IVF, the long-term costs and outcomes of twins and singletons should be determined. To our knowledge this is the first study on both long-term (societal) costs and health outcomes of IVF twins and singletons, allowing us to calculate the long-term cost-effectiveness of several (combinations of) SET and/or DET strategies.

This study will use QALYs as outcome measure, which will enhance comparison with other health care programs and the interpretation of the ICERs. Furthermore, this study will be conducted from the societal perspective and this includes not only hospital costs, but also productivity, patient and family costs. Most previous studies focused on hospital costs only, neglecting costs outside the healthcare sector. Analyses will also be performed from the healthcare perspective.

Another strength of this study protocol is its efficient design. The larger part of the health problems and associated costs will occur in a relatively small group of children. The study is set up such that data collection focuses on these children. Data collection regarding the first year of life is focused on children at high risk of health problems due to a prematurity, a low Apgar score, a congenital malformation or a low birth weight. Data collection regarding the second to fifth year of life is focused on children who experienced health problems during their first life year. Additional advantage is that, due to the decreasing number of participants making up the sample size in later stages of the study, a particularly high level of detail can be reached in the data collection.

Although this study will apply the commonly used QALY as measure of outcome, a number of potential problems are to be expected. The first question is whether the QALY concept is suitable to value QALYs '*generated' *or '*created'*, instead of QALYs *gained*, for which the QALY framework was originally developed. Furthermore, a twin consists of two live-born children. An interesting issue in using QALYs as outcome measure is that a healthy twin will theoretically generate twice as much QALYs as a healthy singleton, which is the total opposite compared to how twins have been valued in cost-effectiveness analyses thus far. As twins are more common among woman receiving DET, including the QALYs of both twin children in the cost-effectiveness analysis will have considerable impact on the ICERs [32]. Furthermore, it can be expected that parents with a single child after SET, will more often undergo subsequent IVF treatment(s) than parents with a twin after DET. As a result, the long-term cost-effectiveness analysis including only the first IVF treatment is of limited value. It does not reflect the real world situation in which parents can opt for up to three IVF treatments. Our secondary analysis including subsequent IVF treatments will take account of this imbalance.

Moreover, when using QALYs, an interesting question is furthermore whether the QALYs of parents and siblings should be taken into account as well. For example, the birth of a (handicapped) child may have a considerable impact on family members. It should be considered, if and how QALYs of the parent and family members should be included in the analysis.

